### *Statistical analysis*

The data will be analysed using Stata14 (StataCorp Texas). All analyses will take account of the cluster trial design, i.e. the clinic/centre is the unit of randomization. The survey suite of commands ("svy") in Stata will be used for all regression models and cross tabulations.

We will first compare the distribution of characteristics between the trial arms including important prognostic covariates such as age, sex, duration of diabetes. The primary outcome will be analysed using Poisson regression comparing the proportion of DR in the TR arm with that in UR and report the risk ratio (RR) and 95% Confidence Interval (CI) in unadjusted analysis and covariate adjusted analysis. These analyses will be undertaken for the ITT and PP populations. The ITT primary outcome analysis will represent the trial main result.

For the secondary outcome we will investigate characteristics associated with hospital attendance using Poisson regression in a model including randomised arm. We will first check whether characteristics of attendance vary by randomised arm in separate analyses before combining in a single model.

We will also report descriptive analyses based on the semi structured interviews. These will be transcribed into a data base and text analysis techniques will be used to group the responses (this may necessitate translation into English if Tamil software is not available).

**Ethical consideration:** The protocol including the procedures for fully informed consent will be presented for approval from the Research Committee and the Institutional Review Board of Aravind Eye Hospital, India. Eligible participants in the telemedicine arm will be given an information sheet in the local language which will explain the purpose of the study and what

procedures are involved and asked for consent to access their clinical records. Patients in the usual care arm will be asked for consent to access their medical records. In both arms patients will be told that they may in future be interviewed for their views about diabetes and DR. Patients will be reassured that their personal and clinical details will be kept confidential and in the telemedicine arm that their usual care will not be affected if they choose not to participate. For patients who are illiterate the information will be read out to them. All participants will be given the information sheet to take home and the contact number of the study co-ordinator. At the next visit of the participant the centre co-ordinator will answer any further questions from the patient and seek written consent (or for illiterate patients, a thumb impression will be taken)

**Benefits of study:** The vision loss due to DR cannot be reversed and hence timely detection of the problem is crucial in preventing advancement of the disease there by saving the vision. This will be possible only by encouraging the patients at risk to undergo fundus examination on a regular basis. Very low rate of detection is the most important challenge in the current scenario. The findings of this study will provide evidence as to which method of case finding is more effective in promoting early detection of DR. The results can be used to promote best practices among the providers and to create awareness in the community to achieve effective management of DR. However, no RCT on telemedicine in DR has been done in India or (as far as we know) in any other country. If telemedicine for DR is effective in the urban/ semi urban environment we will conduct a similar trial in the future in the rural setting.

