A total of eight diabetes centres will be identified and four each will be randomly allocated to each arm stratified by distance from Aravind Eye Hospital Madurai. The aim of stratification is to ensure that there is no imbalance in the randomized arms in proximity to the hospital. The stratification criteria will be <5km, ≥ 5-10km. This covers the most densely populated areas (less than 5km), and the outer peri-urban/rural areas. An interviewer cum counsellor will be appointed at each of the diabetes centres in UR who will administer the consent form, collect patient data and do the referral. In the diabetes centres in TR, the interviewer cum counsellor will also be trained in fundus photography through a structured two-weeks training. The study will be carried out for a period of six months and a window of one month after referral will be given for the patient to visit the eye hospital.

At the end of the one month window after the last referral, those patients who have not complied with the referral will be contacted. A short semi structured interview will be conducted with (i) all those who decline referral and/or imaging to understand the barriers to compliance (ii) a sample of those who do attend Aravind Eye Hospital to understand the drivers of acceptance. The topic guide for the interviews will be developed from previous literature and other studies on barriers and drivers to cataract surgery uptake undertaken by Aravind Eye Hospital [21]. The results from these interviews will form a part of the final overall evaluation of the trial by adding a qualitative component. The interviewer will also ask about any other eye examinations that have been conducted by other eye professionals (ophthalmologists or optometrists) since patients may have chosen to attend elsewhere for the eye examination. In this situation information will be sought on the DR findings.

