**Sample size estimates:**

The following preliminary assumptions were made:

- (i) The proportion of patients in UR diagnosed with DR at AEH is 30% of the referred patients
- (ii) The proportion of patients in TR diagnosed with DR at AEH is 50% of the referred patients
- (iii) Power of 90% and alpha of 0.01 for a 2 sided test
- (iv) The design effect is 2 (derived from reference [4])

The estimated total sample size is 616 patients, equally distributed in each arm. Each of the 8 centres will recruit between 80 and 100 patients eligible for referral to AEH. We anticipate the time taken to recruit this number of eligible patients will be approximately 6 months. This is a conservative estimate because it is likely that a substantial number of eligible patients will be available. Population estimates show that the proportion with DR in diabetics is 12% and is higher in urban areas, in high income groups and in older people (50+) and with longer duration of diabetes [5].

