### *Outcomes*

The primary outcome will be diabetic retinopathy (DR) confirmed by dilated fundus examination at the hospital.

The secondary outcome will be hospital attendance.

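### Separate arm-specific attendance models do not test whether a characteristic's effect differs between arms; interactions in the planned combined model would

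*Protocol*

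**What the plan says.** The Protocol's Outcomes section states: "The secondary outcome will be hospital attendance". Under Statistical analysis, "we will investigate characteristics associated with hospital attendance using Poisson regression in a model including randomised arm". The next sentence sets the order of work: "We will first check whether characteristics of attendance vary by randomised arm in separate analyses before combining in a single model". The same text stands again in the second copy, under the Statistical Plan heading at the end of the document.

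Neither copy names an interaction term or a test of heterogeneity, says what would count as varying by arm, or makes pooling conditional on the result.

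Three other statements set the conditions for these models:
- Of eight centres, "four each will be randomly allocated to each arm" (Study Plan).
- "The survey suite of commands ('svy') in Stata will be used for all regression models and cross tabulations" (Statistical analysis), so each arm-specific model takes its variance from four centres.
- "The estimated total sample size is 616 patients, equally distributed in each arm" (Sample size estimates).

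**The concern.** Whether a characteristic acts differently under telemedicine and under universal referral is a question about the ratio of two risk ratios. Arm-specific models test each risk ratio against 1; nothing in them tests one against the other. Two equal effects can give one small and one large p-value by chance, and two unequal effects can both be significant.

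At stake is any statement that different kinds of patient attend in the two arms. Attendance is the only secondary outcome, and the document intends the trial to inform scaling up and a possible rural trial. A claimed difference in who attends could be carried into that work without having been tested.

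**Working it through.** **Plan's own figure.** The Protocol gives none for this analysis. The sample size is used here only to set the layout.

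**Inputs from the Protocol**
- 616 patients, equal arms: 616 / 2 = 308 per arm; 308 / 4 = 77 per centre.
- Design effect 2: ICC = (2 - 1) / (77 - 1) = 1/76 = 0.013.
- Design degrees of freedom (df): 4 - 1 = 3 in an arm-specific model with no further strata declared (critical t 3.18); 8 - 2 = 6 in a combined model stratified by arm (critical t 2.45).

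**Assumptions not in the Protocol**
- Attendance is 40% in one arm and 60% in the other, or 50% in both.
- There is one binary characteristic with 50% prevalence and the same true risk ratio in both arms.
- Tests are at the 5% level.
- A difference is declared when the characteristic is significant in exactly one arm.

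**Formula.** With powers p1 and p2 in the two arms, P(exactly one significant) = p1(1 - p2) + p2(1 - p1), or 2p(1 - p) when they are equal:
- p = 0.05 (no effect): 2 × 0.05 × 0.95 = 9.5%
- p = 0.30: 2 × 0.30 × 0.70 = 42%
- p = 0.50: 2 × 0.50 × 0.50 = 50%, the maximum
- p = 0.80: 2 × 0.80 × 0.20 = 32%
- p = 0.90: 2 × 0.90 × 0.10 = 18%

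The answer depends heavily on power, so the powers were obtained by simulation for this layout.

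**Simulation.** Log-link Poisson models with centre-robust variance, 1,500 runs per scenario. The Monte Carlo standard error is about 1.3 points near 50% and 0.6 points near 6%. Ranges cover the two attendance assumptions. The true effect is identical in both arms throughout.

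| True RR | Separate models disagree, 4 centres × 77 per arm | Interaction test significant (6 df), 4 centres per arm | Separate models disagree, 22 centres × 14 per arm |
|---|---|---|---|
| 1.0 | 8.9-9.8% | 5.9-6.9% | 8.1-9.8% |
| 1.2 | 30.7-36.6% | 5.7-6.6% | 43.9-45.4% |
| 1.3 | 46.7-48.5% | 6.5-7.2% | 51.5-52.4% |
| 1.5 | 43.3-49.3% | 6.0-7.0% | 14.2-23.5% |
| 1.8 | 22.6-27.3% | 5.8-6.3% | 0.5-2.7% |

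Formula and simulation agree. At RR 1.8 with 40%/60% attendance the simulated powers are 0.744 and 0.969, so 0.744 × 0.031 + 0.969 × 0.256 = 27.1%, against 27.3% simulated.

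If 7 df are used for the interaction instead of 6, with 40%/60% attendance and the same ICC, its error is 6.5-8.1%.

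**Number of centres.** The last column keeps 308 patients per arm (22 × 14) and the same ICC. With more centres, false disagreement falls sharply at RR 1.5 and 1.8 but is higher at RR 1.2 and slightly higher at 1.3. The number of centres acts through power and is not the source of the flaw.

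**When the effects do differ.** With RR 1.0 in one arm and 1.5 in the other, and 50% attendance in both, the separate-model rule flags a difference in 63.5% of runs and the interaction test in 60.9%. At a common RR of 1.5 with the same attendance, they flag 43.3% and 7.0%. In this scenario the interaction test gives up little sensitivity and removes most of the false differences.

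**The case against.** The strongest reply is that the faulty rule is imputed. The Protocol gives a sequence, check and then combine, with no significance threshold and no condition for combining. A reader might infer that pooling hangs on which characteristics reach significance in each arm; the text does not say so. The check could be a descriptive comparison of estimates and intervals. This stands, and every disagreement percentage above is conditional on the assumed rule. It does not rescue the method: comparing two sets of estimates by eye has no defined error rate and is still not a test of their difference.

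Second, the criterion for varying could be left to an analysis plan. Its absence alone would not be a finding. But the Protocol does name the method, separate analyses, and that method does not answer the question it is given.

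Third, a reader might quote a false-difference rate of 40-50% as a property of this trial. That takes powers near the peak of 2p(1 - p). A characteristic with no effect gives only 9-10%, and at 90% power the formula gives 18%.

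Fourth, a reader might blame the four centres per arm. The comparison with 22 centres supports this only from about RR 1.5 upward.

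Finally, looking within arms has a rationale. All universal-referral patients are offered referral, whereas telemedicine patients are referred only after a positive or inadequate image, so the referred groups differ by design. That justifies showing arm-specific results; it does not make them a test.

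**Conclusion.** The point holds, as a minor one. The stated method does not assess whether associations with attendance differ between arms, and a standard alternative fits inside the combined model already planned.

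Under the assumed rule of significance in one arm only, with attendance of 40-60% and the Protocol's layout, equal effects would look different in about 9-10% of cases for a null characteristic and about 23-49% for risk ratios of 1.2 to 1.8. The interaction test errs in about 6-7%, slightly above the nominal 5% because there are only eight centres. These rates would change with other attendance levels, prevalences or decision rules.

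It would be wrong to infer that the trial's conclusion is at risk. The Protocol makes the intention-to-treat analysis of the primary outcome its main result, and that analysis does not use these models. The hypothesis speaks of detection and acceptance rates and makes no claim that predictors of attendance differ by arm.

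**What to change.** Replace the sentence on separate analyses, in both copies, with wording to this effect:

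- Variation by arm will be assessed in the combined Poisson attendance model that includes arm, through a small pre-listed set of arm-by-characteristic interactions, using design-based degrees of freedom (6 when stratified by arm).
- Each interaction will be reported as a ratio of risk ratios with its 95% CI, alongside arm-specific risk ratios taken from the same model.
- Results of separate arm models, if shown, will be descriptive only.
- A non-significant interaction will not be read as proof that the effects are the same.

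The cost is wording; no new data are needed. The drawback is imprecision: eight centres support few interactions and the intervals will be wide, but they will show that uncertainty openly.

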### **Study Plan:**

**Design:** The design is a cluster randomised trial (RCT). Diabetes centres will be randomized to one of two strategies: telemedicine referral (TR) or universal referral (UR). Patients attending diabetes centres within a distance of 10 kms from Aravind Eye Hospital Madurai (i.e. within the urban and peri-urban area) will undergo one of these randomized interventions. A cluster RCT is required to avoid patients in the same centre being offered different screening interventions which might present both logistic and ethical difficulties.

**Procedures:** All patients identified in either arm meeting the inclusion and exclusion criteria will be referred to the clinic study coordinator who will seek fully informed patient consent (see below, under Ethical considerations) prior to enrolling the patient. Those enrolled will be counselled about DM and the importance of vision screening, and will be invited for either digital fundus imaging at the diabetes centre (TR) or for detailed examination for diabetic retinopathy (DR) at an eye hospital (Aravind Eye Hospital Madurai, AEH). Randomisation is at the level of the centre and there is no individual patient randomisation. In TR the diabetes centre will be equipped with a digital imaging system for screening the fundus and the patients diagnosed with DR or probable DR will be counselled to visit AEH for a full retinal examination to confirm (or not) the presence of

DR. In UR, the eligible patients will be counselled and referred to undergo eye examination at AEH. In both the arms the counselling and the awareness creation materials will be standardised.

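### Patients are recruited after centre allocation and the protocol describes fuller study information in TR than in UR; one common consent procedure is needed, with decliners kept in the denominator

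*Protocol*

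**What the plan says.** The Design and Procedures paragraphs of the Study Plan set up a cluster trial: "Randomisation is at the level of the centre and there is no individual patient randomisation". Eligible patients in either arm go to a coordinator "who will seek fully informed patient consent (see below, under Ethical considerations) prior to enrolling the patient". The counsellor at a UR centre is the person "who will administer the consent form, collect patient data and do the referral"; the TR counsellor is also trained in fundus photography. Whoever seeks consent therefore knows the arm.

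The Ethical consideration paragraph, at the end of the Statistical analysis section, then describes the arms separately. For TR: "Eligible participants in the telemedicine arm will be given an information sheet in the local language which will explain the purpose of the study". That sentence goes on to the study procedures and ends with the request for consent: "procedures are involved and asked for consent to access their clinical records". For UR: "Patients in the usual care arm will be asked for consent to access their medical records". The assurance about refusal is also tied to one arm: "in the telemedicine arm that their usual care will not be affected if they choose not to participate".

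Three other items in that paragraph are not arm-specific: notice of a possible later interview, confidentiality, and a later sentence under which every participant takes the information sheet home.

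**The concern.** In a cluster trial with recruitment after allocation, anything that makes agreement to enrol depend on the arm can unbalance the groups being compared. Here the arm-specific text tells TR patients what the study is for, what it involves and that they may stay out at no cost to their care. It describes none of this for UR.

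Willingness to be screened is close to what the trial measures. The hypothesis includes acceptance, the secondary outcome is hospital attendance, and the primary outcome can be reached only by patients who undergo a dilated examination at the hospital. If reluctant patients tend to decline enrolment in TR but are enrolled in UR and then do not attend, the comparison tilts towards TR. The prognostic covariates named in Statistical analysis (age, sex, duration of diabetes) do not measure willingness, so adjusting for them would not be expected to remove the tilt.

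**Working it through.** **1. What each arm is told, according to the Ethical consideration paragraph**

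| Item | TR | UR |
|---|---|---|
| Sheet on purpose and procedures (arm-specific sentences) | given | not mentioned |
| Assurance that staying out does not affect usual care | given | not mentioned |
| Object of consent | access to clinical records | access to medical records |
| Notice of possible interview | yes | yes |
| Confidentiality | yes | yes |
| Sheet to take home (later sentence) | yes | yes |

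The first and last rows cannot both be right for UR. The third row shows that the object of consent is the same in both arms.

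**2. Do other sections settle it?** Only partly. Procedures requires fully informed consent in either arm, but refers to the Ethical consideration paragraph for the detail, so it leads back to the unequal text. The paragraph on the eight centres says that a consent form is used in UR, but not what it covers.

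**3. Order of steps.** Procedures places consent and enrolment first, and the invitation to imaging or to the hospital afterwards. The planned interviews include people who turn down imaging. Refusal after enrolment is therefore foreseen in TR, and refusal of consent is possible in both arms.

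**4. Size, over all enrolled patients.** The plan gives no refusal or consent rate, so it has no figure to reproduce. The following is an illustration. Let each arm have N eligible patients, of whom a share u is unwilling and would yield no confirmed DR. Let both arms truly identify D cases. If the unwilling leave TR before enrolment and all stay in UR:

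- TR proportion = D / [N(1 − u)]
- UR proportion = D / N
- Risk ratio (RR) = 1 / (1 − u), where the truth is 1

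The values of u are assumptions. The UR proportion of 0.30 comes from Sample size estimates:

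- u = 5%: TR 0.30/0.95 = 0.316, RR 1.05
- u = 10%: TR 0.30/0.90 = 0.333, RR 1.11
- u = 20%: TR 0.30/0.80 = 0.375, RR 1.25

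If unwilling patients also refuse in UR, the factor is the UR consent rate divided by the TR consent rate. It is 1 when the two rates are equal.

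**5. Size, in the planned ITT set.** Strategies of analysis counts every UR patient, because all are offered referral. In TR it counts only those referred after imaging (further investigation needed, or image inadequate). A TR patient who refuses consent is outside that set, and so is one who enrols and then declines imaging. For patients who would not have been imaged anyway, loss at consent adds nothing to an asymmetry that the ITT rule already creates. Consent can still act inside the planned set in one way: TR patients who agreed after fuller information may be likelier to attend when referred.

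**The case against.** The strongest reply is that this is only untidy wording. Informed consent is required in both arms, a consent form is used in UR, interview notice is given in both arms, and every participant takes the sheet home. Enrolment precedes the offer of imaging, and any patient may refuse. On that reading consent is already equal. Much of this stands: the document contradicts itself and does not plainly fix an unequal procedure. It does not dispose of the point, because the only paragraph with the detail separates the arms, and staff at eight centres could follow either version.

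Three stronger readings are tempting, and the documents do not support them:

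- A reader might infer that TR patients consent to the study procedures and UR patients only to use of their records. The text asks for record access in both arms.
- A reader might infer that unwilling patients necessarily leave TR at consent and remain in UR. This is stated nowhere, and the order of steps allows them to enrol in TR and decline later.
- A reader might apply the 1.05 to 1.25 inflation to the trial's main result. It belongs to an all-enrolled denominator that the plan does not use at present.

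It might also be argued that patients should sign before learning what their centre offers. That sits badly with fully informed consent and with TR centres visibly equipped for imaging, and the remedy does not need it.

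**Conclusion.** The point holds as an inconsistency that opens a plausible recruitment bias in favour of TR. The protocol describes different information by arm, given after allocation by staff who know the arm, and contradicts this within the same paragraph. The asymmetry lies in what patients are told; the object of consent is the same.

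The size is unknown. The factor of 1.05 to 1.25 assumes that 5% to 20% of eligible patients are lost from TR only, that none of them would have had DR confirmed, and that the denominator is all enrolled patients. It shows how the bias scales and is no estimate for this trial.

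The larger imbalance, with unwilling patients uncounted in TR and counted as non-cases in UR, comes from the ITT definition. Equal consent alone would not cure it, and correcting the ITT definition alone would leave any loss before enrolment in place. The two changes belong together.

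**What to change.** - Reconcile Procedures, the paragraph on the eight centres and the Ethical consideration paragraph to one information sheet and one consent form, with the same content and the same assurance about usual care in both arms. Both should be completed before imaging or referral is offered.
- Keep every enrolled patient in the primary denominator of both arms, including those who decline imaging or referral. Amend Strategies of analysis in both places where it appears (Data preparation and analysis, and Statistical Plan).
- Report the numbers approached, refusing and enrolled by arm and centre, so that any difference in recruitment can be seen.

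The cost is rewording, ethics approval of a common form, and a separate agreement to imaging in TR. The new denominator also has a planning consequence. The 30% and 50% in Sample size estimates are proportions of referred patients. The UR figure carries over because all UR patients are referred, but the TR figure must be restated per enrolled patient and the sample size recalculated.
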